## Abstract

**Introduction:**

Sexual health is essential for general health and well-being. Sexual health services for middle-aged and older adults are not prioritised and optimising available services for this population is often overlooked. Not much is known about preferences for accessing sexual health services among middle-aged and older people or level of satisfaction with current services. The aim of this study is to explore preferences for seeking sexual health services among middle-aged and older adults in the UK. This study will use discrete choice experiments (DCEs) including initial qualitative interviews followed by the survey, which have been used as a tool to explore preferences in various health service delivery.

**Methods and analysis:**

The project will be carried out in two phases. First, we will conduct in-depth semi-structured interviews with 20–30 adults (aged 45+), including disabled people, and those from sexual minority groups resident in the UK. Interviews will explore indications, preferences and factors related to accessing sexual health services. Themes and subthemes emerging from the analysis of the interviews will then be used to design the choice sets and attribute level for the DCEs. For the second phase, for the DCEs, we will design choice sets composed of sexual health service delivery scenarios. The software Ngene will be used to develop the experimental design matrix for the DCE. We will use descriptive statistics to summarise the key sociodemographic characteristics of the study population. Multinomial logit, latent class and mixed logit models will be explored to assess sexual health service preferences and preference heterogeneity.

**Ethics and dissemination:**

Ethical approval for both parts of this study was granted by the Research and Ethics Committee at the London School of Hygiene & Tropical Medicine. Findings from this study will be disseminated widely to relevant stakeholders via scheduled meetings, webinars, presentations and journal publications.

Strengths and limitations of this studyThis is the first discrete choice experiment (DCE) exploring preferences for sexual health services among middle-aged and older adults including disabled people.Our DCE is designed based on detailed formative research whereby choice sets are developed from emerging themes from 21 semi-structured interviews.While the survey targets mature adults (age 45 and older), we sought to ensure inclusion of those from sexual minority groups and disabled people by recruiting from local community-based organisations. This is to ensure diversity within this population to allow for subanalysis.Recruitment will be restricted to only adults aged 45 and older and living in the UK as a result, generalising the findings may be restricted to only the UK or other places with similar settings.

## Introduction

Sexual health is an integral part of health, well-being and quality of life. However, many existing sexual health programmes, interventions and research are tailored for youth and younger adults.^1^ The sexual health needs of middle-aged and older adults are often neglected, including by health professionals.^2^ There are also a host of diverse challenges and barriers that interplay in how and why this age group access sexual health services. Older adults are increasingly experiencing higher rates of comorbid illnesses further complicating their sexual health and well-being. Up to 9% increase in sexually transmitted infections among adults aged 50 and above have been reported. The rate of HIV infections is increasing faster among people aged 50 and above than in the under 40s, consequently, the number of people aged 50 and over living with HIV has now doubled in the last decade.^3 4^ Older adults typically turn to family and friends to seek support for health needs and a study assessing sexual health clinic attendance in Britain found that non-attendance was higher among older adults.^5 6^ Accordingly, there is suboptimal uptake of sexual health services among middle aged and older adults.^7 8^ Within the broader group of ‘older people’, certain groups may be particularly neglected, such as disabled older people, as they face additional barriers to accessing health services.^9^ This is an important issue, as almost one in five people in the UK are aged 65+, and 42% of people in this age group report a disability.^10^ Disability is defined under the Equality act of 2010 as having a physical or mental impairment that has substantial and long-term negative effect on the ability to do normal daily activities.^11^ Despite the growing population of middle-aged and older adults and an increasing body of evidence suggesting sexual health is important to quality of life, there is limited evidence to support preferences and tailor services for specific groups within this population.^12 13^

This study will explore preferences for seeking sexual health services among middle-aged and older adults. This is part of a larger study to inform areas for improved sexual health services for adults aged 45 and above, including disabled ones and from sexual minority groups living in the UK. We have chosen 45 years as our cut-off age as menopause, erectile dysfunction and other sexual health issues become more common in that age group. Our study findings will explore issues related to service uptake and identify strategies to increase the uptake of sexual health services among adults aged 45 and above in the UK.

Discrete choice experiments (DCEs) are a quantitative approach to measure strength of preferences. It is an attribute-based measure of utility, based on the assumptions that healthcare interventions, services or policies, can be described by their attributes and that user preferences depend on the levels of these attributes.^14^ DCEs ask participants to make choices from hypothetical alternatives. They are increasingly used in health research to study patient and/or physician preferences.^15^ For instance, DCEs have been used to determine preferences for HIV prevention and testing among a range of specific populations and settings to inform strategies for optimising health services.^16–21^ DCEs have also been employed to study preferences for social care among older adults.^22^ However, to date, no DCE studies have been conducted to determine preferences for sexual health services among older adults. Our study will use DCEs to explore preferences for accessing sexual health services and any heterogeneity that exists among middle-aged and older adults in the UK.

### Overall aim and objectives of this study

The main aim of this study is to identify strategies to improve access of sexual health services among adults aged 45 and above including sexual minorities and disabled people, in the UK. Specific objectives include:

To identify barriers and facilitators for accessing sexual health services among adults aged 45 and above including sexual minorities and disabled people, in the UK using semi-structured interviewsTo explore key preferences for accessing services for sexual health among middle-aged and older adults in the UK using a DCE survey.

## Methods and analysis

### Overview of approach and methods

The research will be conducted in two phases. First, we will organise semi-structured interviews with adults aged 45 or above to better understand their preferences and the importance of sexual health service and message sharing attributes in influencing their use of these services. Interview data will be analysed thematically, and emerging themes will inform which attributes and levels will be included in the choice sets for the DCEs.

### Patient and public involvement

A key part of this study is community engagement as all studying findings will be dependent on response and input from the community members. With the aim of improving access to services, resulting strategies and solutions will be well received and more sustainable with sound community input. Consequently, community representatives have been recruited and engaged in the study design through local community-based organisations and reaching out through general practitioner (GP) service. Community-based organisations contacted where those specifically providing services to middle aged and older adults, disabled people and those from sexual minority groups. These will be continuously engaged in our survey distribution and participant recruitment, data interpretation, reporting or dissemination plans of our research.

### Phase I—semi-structured interviews

DCEs are increasingly being recommended in health research to explore patient and public preferences.^22^ This includes undertaking a conjoint analysis where related characteristics will be identified early on using literature reviews, group discussions or individual interviews.^23^ First, we will conduct between 20 and 30 semi-structured individual interviews with adults aged 45 and above and stop when data saturation is reached. This formative qualitative research will identify factors that are considered in the decision-making processes among this population related to sexual health services (eg, awareness, location, access process, quality of care or qualifications of healthcare providers, cost), identifying barriers and facilitators to service usage and sexual health message sharing based on older adults’ perceptions of and/or experiences with sexual health services and interaction with sexual health messages. We will also field test the questionnaire using cognitive interviews prior to official start to help us understand how older individuals mentally process and respond to survey questions and DCE choice sets.

Participants will be purposively selected across different locations, age range, ethnic backgrounds and disability status. Recruitment will be via community-based organisations. We will create and disseminate a simple survey to collect data on profile including age, gender, ethnic background location in the UK, sexual orientation, relationship and disability status. We will reach out to community-based organisations to disseminate this survey within their members and networks. From the responses received we will then contact participants purposively selected to ensure good spread and diversity in the sample recruited for interviews. Interviews will be conducted via telephone calls or teleconference using Zoom, Skype or Microsoft Teams and facilitated by an experienced qualitative researcher. Teleconference calls may be either audio or video according to participant preferences. Interviews will be conducted using a topic guide (see online supplemental appendix 1) and we will aim for approximately 30 min per interview session. Adjustments will be made as needed to promote the inclusion of disabled persons (eg, use of sign language interpretation, simple language, inclusion of breaks). Each participant will receive an honorarium worth £30 in appreciation for their participation. A consent form will be provided to participants via email, which will be signed and returned before the interview commences. Verbal consent will also be obtained right at the start of the interview. Interviews will be audio-recorded following participant consent and transcribed verbatim prior to analysis.

10.1136/bmjopen-2022-066783.supp1Supplementary data

### Qualitative data analysis

We will undertake thematic analysis of the qualitative interview data using NVivo. A codebook will be developed both inductively and deductively to guide analysis. We will employ a framework approach and transcribe all interviews verbatim then commence coding of each transcript. Codes will be aggregated to build up the emerging themes. Outcomes of qualitative data analysis will be the indications and use of sexual health services, preferences and factors affecting their decision-making to seek intimate and/or sexual relationships, barriers and facilitators to sexual health service usage. This qualitative data generated will be used to inform the DCE survey to be disseminated to participants in phase II. We will also disseminate the data as presentations in scientific conferences and publications in open access journals (see online supplemental appendix II for some preliminary results).

### Data management

All data (qualitative and quantitative) collected during the course of the research will be stored and managed securely online using our institute’s Open Data Kit (ODK) at the London School of Hygiene & Tropical Medicine (LSHTM). An ODK server hosted at LSHTM allows researchers to submit de-identified data electronically from anywhere in the world to a safe and secure server environment that is hosted on our institutional information technology infrastructure. The identity of participants will be known by the researchers who will assign participant numbers to anonymise responses. Responses will be de-identified prior to analysis, and results will be reported at an aggregate level, individual quotes when used will be followed by participant assigned numbers so that participants cannot be identified.

### Phase II—discrete choice experiment survey

Second, we will use the qualitative information from Phase I to inform what attributes (characteristics) and levels (choices) will be included in the unlabeled choice set, which will be administered in an online survey to a sample of older adults to identify their preferences for accessing sexual health services. We will design choice sets composed of hypothetical sexual health service delivery scenarios. Similarly, as stated for the interview, we will employ the same strategy to recruit disabled people and people from sexual minority groups for the survey to allow subanalyses of the results. We will aim to have disabled people and sexual minorities make up 10% each out of the total sample size.

### Developing the DCE design

#### Pictorial representation of attribute levels and DCE choice set size

A ranking exercise will be organised with some of the interview participants to align and finalise the attributes and levels that will be included in the final choice sets (online supplemental appendix III). After attributes and levels have been finalised, we will generate visual graphics to represent each attribute level in the DCE survey (see online supplemental appendix IV for a sample). To ensure that the visual graphics effectively represent the intended meaning of each attribute level (ie, construct validity), we will conduct qualitative think-aloud, pilot exercises with up to 10 individuals from the target population, including disabled people and those from sexual minority groups and participants will provide feedback about how they interpret and feel about the graphics.^24^ This will be an iterative process with the draft pictorial concepts being tested until they are appropriately representing the intended concept. DCE surveys tend to present between 4 and 18 choice sets. During these interviews, we will also explore the optimal number of choice sets to present to each respondent to manage potential cognitive fatigue. Similar to the phase 1 interviews, participants will be purposively selected across different locations, age range, ethnic backgrounds and disability status. Again, reasonable accommodation will be made to promote inclusion of disabled persons, although people with severe cognitive/intellectual impairment will not be included in this step. Recruitment will be through collaborations with community-based organisations with which our research team already have existing research collaborations with.

#### Experimental design

After visual graphics of the attribute levels have been finalised, we will use the software Ngene to develop the experimental design matrix for the DCE pilot.^25^ For the pilot test, no assumptions about the parameter estimates will be made. We will then specify the appropriate number of attributes, levels, alternatives, blocks and choice sets, and Ngene will iteratively generate design matrices of increasing statistical efficiency. We will use the design with the lowest D-error generated by Ngene. An example of a choice set and DCE design is presented in figure 1. Graphics will have alt-text enabled so that they can be accessed by people with visual impairments.

**Figure 1 F1:**
[figure not shown]
Fictitious example of a choice set. GP, general practitioner

#### Blocking and randomisation of choice set ordering

Depending on the total number of choice sets in the DCE design, choice sets may be grouped into blocks. Respondents will then be randomly assigned to one of the blocks and asked to complete all choice sets in their block. We anticipate using between 4 and 10 blocks, with each block containing 4–10 choice sets. To guard against potential ordering effects, the order of the choice sets within each block will be randomised for each participant.

#### Pilot testing

We intend to use convenience sampling to recruit up to 30 participants for the pilot test. Participants in the pilot test will receive a £20 gift card for completing the survey. Conducting the pilot test will serve two purposes: (1) identify potential problems with the DCE and survey in general (eg, cognitive fatigue or incoherent questions or lack of accessibility) and (2) generate priors (ie, parameter estimates) that will be used to develop the design of the final full-scale DCE. We will analyse the pilot data with multinomial logit (MNL) models, given the limited sample size. Priors from the pilot test will be input into Ngene to finalise and enhance the efficiency of the full-scale DCE design.

#### Full-scale DCE survey

Community-based organisations, local clinics, GP practices and older people care homes will be contacted to help distribute the online survey. Recruitment will be carried out purposively from urban and suburban areas, evenly spread across varying gender mix and the middle age and older adults age groups. We will create formats for completing the DCE surveys both online and offline.

### Eligibility criteria

We will recruit persons who meet all of the following criteria:

Adult aged 45 years or older.Had the experience of accessing sexual reproductive health service’, prior to this study.Resident in the UK for at least 6 months.Willing to consent to participation.

With consent, participants of the DCE will be entered into a draw where up to 20 participants will be randomly selected to receive a £100 gift card.

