### Statistical analysis

We will use descriptive statistics to summarise the key sociodemographic characteristics of the study population. We will assess sexual health service preferences and preference heterogeneity using MNL, latent class and mixed logit (MXL) models. While the MNL is the starting point for most discrete choice models, it suffers from some unrealistic assumptions, particularly around unobserved heterogeneity. The MXL model can accommodate unobserved heterogeneity. The MXL analysis will be conducted with 1000 Halton draws and will assume normally distributed preference heterogeneity for each attribute level. We will assess for unobserved heterogeneity by examining the statistical significance of the SD of the random parameters in the MXL model. We will calculate the relative importance and predicted probabilities of opt-out for select sexual health service scenarios. We will assess how sexual health service and message sharing preferences could vary among those willing and unwilling to use sexual health services by using interaction terms for sociodemographic characteristics.

We will perform latent class analyses to elucidate if there are unobserved groups of people with similar preferences for use of sexual health service.^27^ First, we will conduct a latent class conditional logit model that includes individual characteristics and attribute level preferences.^27^ Selection of individual characteristics will be determined by expert opinion and findings from the formative qualitative interviews. Second, we will determine the optimal number of subgroups by comparing the Bayesian information criterion (BIC) values of 2, 3, 4, 5, 6 and 7-class models and each models’ interpretability and class size distribution.^27^ Lower BIC values indicate better model fit. Third, we will use descriptive statistics to characterise each class based on their members’ preferences and characteristics. All analyses will use effects coding and be weighted to reflect the population of middle-aged and older adults in the UK.

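### The DCE admits only people who have already used a service, but its aim, opt-out estimates and weighting claim to represent all UK adults aged 45 and over

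*Protocol article*

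**What the plan says.** **Who can enter.** The Eligibility criteria section opens with "We will recruit persons who meet all of the following criteria", and one of its four criteria is "Had the experience of accessing sexual reproductive health service", before this study. The section follows the description of the full-scale survey. The sentence after the list says that "participants of the DCE will be entered into a draw", so the criteria govern the DCE.

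**What the study is for.** The Introduction gives as its rationale that "there is suboptimal uptake of sexual health services among middle aged and older adults" and that, in one British study of clinic attendance, "non-attendance was higher among older adults". It then says the findings will "identify strategies to increase the uptake of sexual health services among adults aged 45 and above in the UK". The aims section says: "The main aim of this study is to identify strategies to improve access of sexual health services among adults aged 45 and above".

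**What will be estimated.** The sample size section is built on a population probability of choosing a service over opting out. The Statistical analysis section and the section on relative importance and opt-out plan predicted opt-out probabilities for selected scenarios. All analyses are to be weighted to the UK middle-aged and older population. The analysis section also promises: "We will assess how sexual health service and message sharing preferences could vary among those willing and unwilling to use sexual health services". The stated means is interaction terms for sociodemographic characteristics.

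**What is acknowledged.** The strengths and limitations list names age and UK residence as limits on generalisation. It does not mention prior use, and the protocol gives no reason for the criterion.

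**The concern.** Three parts of the plan refer to different populations. Eligibility defines people with past service contact. The aim and the weighting target are all UK adults aged 45 and over. The sample size calculation speaks of a population probability of uptake over opt-out.

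The variable that separates these populations is past use of a service, and a main reported quantity is the choice of a service over none. Selection is therefore on a characteristic plausibly related to the outcome. Weights can rebalance groups that are in the sample, such as age bands or sexes. They cannot stand in for a group whose inclusion probability is zero. A reader of the weighted results would take the opt-out probabilities, and the preferences behind them, to describe the UK population of this age, when they describe only those whom services have already reached.

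The willing-versus-unwilling comparison has a related but separate weakness. Interactions with age, sex and similar variables estimate differences by those variables. By themselves they do not estimate a difference by willingness.

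**Working it through.** **1. The plan's own figure.** Inputs from the sample size section: p = 0.5, r = 8 choice sets, a = 0.05, 95% confidence (z = 1.96).

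n = (1 − p)/(r·p·a²) × z² = 0.5/(8 × 0.5 × 0.0025) × 3.84 = 50 × 3.84 = 192.1

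The protocol states 191, so the figure reproduces to within rounding. At the target of 240, the same equation gives a = 1.96 × √(0.5/(8 × 0.5 × 240)) = 0.045. That precision is around the opt-out rate of prior users only. More participants narrow the interval but leave the selection in place.

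**2. The bias.** Let s be the share of never-users in the target population, and o_user and o_non the opt-out probabilities in the two groups.

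- Target: s·o_non + (1 − s)·o_user
- What a users-only sample estimates: o_user
- Bias: o_user − target = −s·(o_non − o_user)

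The protocol gives none of s, o_user or o_non. The values below are assumptions, chosen to show the range.

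| s | o_user | o_non | Target | Bias |
|---|---|---|---|---|
| 0.05 | 0.20 | 0.30 | 0.205 | −0.005 |
| 0.20 | 0.20 | 0.30 | 0.22 | −0.02 |
| 0.40 | 0.20 | 0.40 | 0.28 | −0.08 |
| 0.60 | 0.20 | 0.60 | 0.44 | −0.24 |
| 0.60 | 0.30 | 0.30 | 0.30 | 0 |
| 0.60 | 0.40 | 0.30 | 0.34 | +0.06 |

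The bias passes 5 points when s × (o_non − o_user) exceeds 0.05. With s = 0.5 a gap above 0.10 is enough. With s = 0.2 the gap must exceed 0.05/0.2 = 0.25. With s = 0.05 it would have to exceed 1, which is impossible.

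**3. Precision if never-users are added within 240.** Under Equation 1 with an even split of 120 per group, a = 1.96 × √(0.5/(8 × 0.5 × 120)) = 0.063. With only 24 in one group, a = 0.141 there. Holding the planned 191 in each group would need 2 × 191 = 382.

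These figures follow the protocol's reading of a. Equation 1 as printed scales a relative to p, so at p = 0.5 the absolute margins are half as large (0.025 for a = 0.05; about 0.032 for a = 0.063). The conclusion does not depend on which scale is used.

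**The case against.** The strongest defence has five parts.

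- **Direction and size are not in the documents.** A reader might infer that opt-out will certainly be understated and uptake overestimated. The protocol gives no opt-out rate by prior use. The bias is zero if the groups behave alike, and it reverses if never-users opt out less. The criterion is also undefined: it has no look-back period and it includes reproductive as well as sexual health services. Read broadly, it might exclude few people aged 45 and over. This stands, and it limits the claim to a likely direction and an unknown size.
- **Non-attenders are not all never-users.** Lapsed, infrequent and dissatisfied users remain eligible, and uptake can be raised among them. It would be wrong to say that the DCE leaves out everyone who faces barriers. This stands.
- **Barriers belong to Phase I.** The objectives assign barriers and facilitators to the interviews, which seek perceptions as well as experience, and nothing shows that the prior-use rule applies there. Never-users can therefore shape the attributes. This stands, but it does not put their choices into the DCE estimates that are weighted to the population.
- **Experience may be wanted so that choices are informed.** That is a legitimate design, but the protocol does not say so, and it describes DCEs as using hypothetical alternatives. If it is the reason, the target population has to be narrowed to match.
- **Willingness is not prior use.** An experienced user may be unwilling and can choose opt-out. The questionnaire and full model specification are not shown, so the documents do not support saying that the contrast will never be estimated. They support only that the interactions named do not estimate it by themselves.

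**Conclusion.** The point holds as a mismatch between eligibility, target population and weighting. Never-users cannot enter the DCE, so the weighted opt-out and preference estimates cannot represent UK adults aged 45 and over, and the limitations do not say so. This conclusion needs no assumed number.

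Opt-out is likely to be understated, on the assumption that people who have never used a service are less inclined to choose one. The size equals the never-user share times the opt-out difference. It could be under 1 point or well above the planned ±5 points, and the documents do not allow a choice between these. The formula covers opt-out only; any distortion of attribute preferences is not quantified here. A preference study confined to prior users would be valid if it were described as one.

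**What to change.** Choose one of two routes before recruitment, because people who were never sampled cannot be recovered afterwards.

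1. **Widen eligibility.** Remove the prior-use criterion for the DCE. Ask ever/never use before the choice tasks, interact it with the opt-out constant, and report opt-out by prior use. Weighting on sociodemographics alone would not fix the user/never-user mix of a purposive sample. A pooled figure therefore needs an outside estimate of the never-user share, or should give way to the by-group results. Cost: one eligibility line, one question and an ethics notification. Some respondents will judge services without experience, and by-group estimates are less precise: about ±0.063 with 120 per group under Equation 1, and worse in the smaller group if the split is uneven.
2. **Narrow the claims.** Keep the criterion and define which services and what period count. Restrict the opt-out claims, conclusions and weighting target to people with prior use, and add the restriction to the limitations. Cost: text only, but the study then says little about people who have never reached a service.

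Under either route, add a willingness question asked before the choice tasks and use that variable for the willing-versus-unwilling comparison. Cost: one question and the corresponding interaction terms.
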